### The survey

The survey (paper and online versions) will collect quantitative data on individuals’ behaviours, attitudes and ecological characteristics, including social network data to explore the influence of family and peers. Therefore, while the participants are the source of all information, there are two different sampling units: the individual respondent; and the relationships/networks [98]. Objectives of the survey will include the domains; demographics; socio-economic status, and will explore:

•factors that influence smoking, including cultural and social beliefs and attitudes related to smoking, smoking cessation and non-smoking;

•attitudes, knowledge, beliefs and awareness in relation to smoking behaviours;

•nicotine dependence (Fagerström Test for Nicotine Dependence) [83,84];

•the impact of tobacco control programs and campaigns, including awareness and recognition;

•smoking, quitting and non-smoking behaviours; and

•family, friends and peers influence in relation to smoking behaviours.

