### Social network analysis

A network is a structure made up of nodes (individuals, organisations, etc) that are connected together by ties (relations such as friendship, kinship, exchanges, activities, etc) [53-55]. Social network analysis provides a way of characterising and investigating such structures, including through network visualisation (using graphic display as illustrated in Figure 2), structural analysis and statistical analysis [55-58]. If participants' networks influence smoking behaviours, it would be expected that participant’s networks would share similar smoking behaviours. Thus, we would compare the observed network to a simulated network with the same network characteristics, including the same overall rate of smoking prevalence, but with the incidence of smoking randomly distributed across the network [59]. If clustering is occurring among smokers or non-smokers, then the probability that a participant who smokes has a network contact who is also a smoker should be higher in the observed network than in the simulated network [21,60]. Perceived proportion of peers who smoke will be measured by analysing the respondents’ perceptions of how many of their peers smoke (about what proportion (%) of your friends and acquaintances use tobacco?) and respondents’ perceptions of how many of their five closest friends and family are regular smokers (thinking about your five closest friends and family, how many of these five are regular smokers?).

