### Data collection instruments: survey, interview guide and focus group guide

The data collection instruments were developed based on valid, reliable and tested surveys, including the:

•Australian Census;

•Fagerström Test for Nicotine Dependence;

•National Aboriginal and Torres Strait Islander Social Survey questionnaire;

•National Aboriginal and Torres Strait Islander Health Survey questionnaire; and

•National Drug Strategy Household Survey questionnaire [2,83-88].

The network analysis components are adapted from previous studies of social networks by Alexander et al. [89], De Lange et al. [90] and others [14,90-94]. Each instrument includes social network questions in relation to the characteristics of the participants’ friends, family and people that reside in their household. The data collected, including responses to the network questions, will provide invaluable insight into the centrality of participants, their relationships/networks and smoking behaviours and beliefs. Network analysis will also be supported through recruitment via convenience and snowball sampling.

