Social network analysis will be used to assess if individuals' social networks influence smoking behaviours. Network analysis will include exploring smoking and non-smoking networks constructed from the survey data and complemented by the qualitative data collection. This will include network visualization, structural analysis and statistical analysis [55]. Several network level measures of structure will be assessed, including clustering, network size, number of ties and reciprocity [55,58]. To study the clustering of smoking behaviour, we will compare the observed network at each data collection point to a simulated network with the same network characteristics, including the same overall rate of smoking prevalence, but with the incidence of smoking randomly distributed across the network [59]. If clustering is occurring among smokers or non-smokers, the probability that a participant who smokes has contact with other smokers should be higher in the observed network than in the simulated network [21,60]. These network metrics will be used to provide a descriptive presentation of the network/s and any changes over time. The pre- and post-test survey will be analysed using Analysis of Variance (ANOVA) on the gain scores and Analysis of Covariance (ANCOVA).

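### The random-scatter reference for smoking clustering does not isolate the link between a respondent's smoking and that of the contacts the respondent reports

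*Protocol article*

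**What the plan says.** All places are in the protocol article.

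- **The survey:** "while the participants are the source of all information, there are two different sampling units: the individual respondent; and the relationships/networks".
- **Data collection instruments:** every instrument asks participants about the characteristics of "friends, family and people that reside in their household".
- **Social network analysis (Background):** peer smoking is measured by the respondent's own perception, as a percentage of friends and acquaintances and as a count among the five closest friends and family.
- **Social network analysis and The survey, Analysis:** the observed network is compared with a simulated one that keeps the network characteristics, "including the same overall rate of smoking prevalence, but with the incidence of smoking randomly distributed across the network". The criterion is directional: if there is clustering, "the probability that a participant who smokes has contact with other smokers should be higher in the observed network than in the simulated network".
- **The survey, Analysis** gives this work two purposes. One is inferential: "Social network analysis will be used to assess if individuals' social networks influence smoking behaviours". The other is not: "These network metrics will be used to provide a descriptive presentation of the network/s and any changes over time". No significance level, p-value or rejection rule is given.

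**The concern.** When a respondent describes several friends, relatives or household members, those descriptions form a set belonging to that respondent. Members of a set may be alike because they share a household, because they know each other, or because the respondent tends to report high or low in general. None of this requires a link with the respondent's own smoking.

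Scattering smoking freely over everyone changes two things besides that link:

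1. It makes the members of each set independent of one another.
2. It gives respondents and contacts the same expected prevalence, although one is self-reported and the other is perceived.

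The observed network still carries both features. A gap between observed and simulated can therefore arise with no respondent-contact link, or a real link can be hidden. Drawing more simulated networks does not help, because each draw removes the same features. At stake is the answer to research question 1, whether social networks influence smoking.

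**Working it through.** **Inputs from the article.** 102 respondents (the stated minimum) and 36% smoking (the pre-intervention rate), both from the survey's Sample size section; 5 contacts, from the five-closest item. The article gives no error rate or power for the clustering comparison, so there is no figure of its own to reproduce.

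**Assumed, because the article gives no value.** Within-set correlation (ICC) from 0 to 0.5; contact prevalence equal to 36% unless varied; a one-sided 5% level, used only to express the size of the error. In every setting of steps 1 to 3, contacts' smoking is independent of the respondent's own smoking.

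**1. Share of smokers' contacts who smoke: spread.** Likeness within a set multiplies the variance of the share by about 1 + (k - 1) x ICC. With k = 5 this is 1.4, 1.8 and 2.2 at ICC 0.1, 0.2 and 0.3. The scattered reference lacks this factor. The approximate chance of exceeding its upper 5% point is 1 - Phi(1.645 / sqrt(factor)):

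- ICC 0.1: 1 - Phi(1.390) = 8.2%
- ICC 0.2: 1 - Phi(1.226) = 11.0%
- ICC 0.3: 1 - Phi(1.109) = 13.4%

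Monte Carlo results (beta-binomial contacts, ties fixed, 2,000 studies x 400 relabellings):

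| ICC | Scattered, 5 contacts | Scattered, 10 contacts | Sets kept whole, 5 contacts |
|---|---|---|---|
| 0 | 5.1% | 4.4% | 4.1% |
| 0.05 | 6.5% | 7.6% | 4.6% |
| 0.1 | 6.4% | 9.8% | 3.8% |
| 0.2 | 10.2% | 14.2% | 4.2% |
| 0.3 | 12.7% | 18.9% | 4.6% |
| 0.5 | 16.8% | 22.6% | 4.7% |

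In the last column, respondents' status is permuted and each contact set stays intact. At ICC 0 the scattered reference is correct.

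**2. Share of smokers' contacts who smoke: centre.** Scattering over one respondent and five contacts centres the reference near (36% + 5 x contact prevalence) / 6, while the no-link value is the contact prevalence itself.

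- Contacts at 26%: (36 + 130) / 6 = 27.7%, which is 1.7 points too high. Clustering is flagged in 0.6% of studies.
- Contacts at 46%: (36 + 230) / 6 = 44.3%, which is 1.7 points too low. Clustering is flagged in 21%.

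Both rates are at ICC 0. With sets kept whole they are 4.0% and 4.8%. (The 46% setting used 1,000 studies x 300 relabellings.)

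**3. The other reading: having at least one smoking contact.** The wording allows this too. Under independence the value is 1 - 0.64^5 = 1 - 0.107 = 89.3%. For a beta-binomial with s = (1 - ICC)/ICC and b = 0.64 s, the chance of no smoker among five is the product of (b + i)/(s + i) for i = 0 to 4:

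- ICC 0.1: 0.640 x 0.676 x 0.705 x 0.730 x 0.751 = 0.167, so 83.3% have one
- ICC 0.2: 0.640 x 0.712 x 0.760 x 0.794 x 0.820 = 0.226, so 77.4%
- ICC 0.3: 0.640 x 0.748 x 0.806 x 0.843 x 0.867 = 0.282, so 71.8%

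Here the reference sits 6 to 17.5 points above the true no-link value, so a real link would tend to be missed. The two readings err in opposite directions.

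**4. Limit of the alternative.** If smokers wrongly report 5-20% of their non-smoking contacts as smokers (assumed), permutation with sets kept whole still flags clustering in about 11-86% of studies, at ICC 0 or 0.2. It does not remove reporter bias.

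**The case against.** **No formal test is stated.** The metrics are described as a presentation of the network and its changes. This stands: the percentages above belong to an illustrative rule, and a reader who concluded that a specified test has an inflated error rate would go beyond the text. The same section nevertheless uses the analysis to assess influence and gives an observed-versus-simulated criterion, so a reference with the wrong spread or centre can mislead without a p-value.

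**Contacts may be respondents too.** Recruitment is partly by snowball, and reciprocity, which needs reports from both ends of a tie, is among the listed measures. This also stands. It is tempting to say that every contact is described by one respondent only; the article does not say so, and the extent of overlap cannot be known from it. For ties between two self-reporting respondents, whole-network relabelling is suitable, and keeping sets intact while permuting status would not be possible. The perception items remain one-reporter data.

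**Random labelling with ties fixed is a valid null.** It is, for no clustering of any kind with one common prevalence. Research question 1 asks something narrower.

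**Likeness usually includes the respondent.** If the respondent shares the circle's likeness, there is a real link and the choice of reference matters little: in a check with 5 contacts, detection was 56% with the scattered reference against 50% with sets kept whole at ICC 0.1, and 99.8% with both at ICC 0.3. The harm lies where contacts resemble each other more than they resemble the respondent, or where prevalences differ.

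**Other analyses exist.** The survey's Analysis section lists rank tests, rank correlations and regression, which could be applied to the peer items, though it does not assign them. One cannot say that the simulation is the only route to question 1.

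**Conclusion.** The concern holds in a limited form. For respondent-reported contacts, the stated reference answers whether there is any clustering under one common prevalence. It does not answer whether a respondent's smoking is linked to that of the contacts. It is correct when contacts within a set are uncorrelated and prevalences are equal.

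Under an assumed ICC of 0.1-0.3 with 102 respondents and 5 contacts, the share statistic is flagged in about 6-13% of no-link studies at an illustrative 5%. The any-smoking-contact reading is centred at 89% against a true 72-83%. Unequal prevalence alone moves the flag rate from under 1% (contacts at 26%) to 21% (contacts at 46%). The article supplies neither the correlation nor the contact prevalence, so the actual error cannot be fixed. Its own premise that behaviours are shared within networks makes zero correlation unlikely.

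A reader might infer from the sentence on two sampling units that relationships are claimed to be statistically independent. It does not say that; it distinguishes two levels of data and is only the premise here. The weakness lies in the simulated reference itself.

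**What to change.** - In Social network analysis and in the survey's Analysis section, state that for respondent-reported contacts each respondent's reported set (ties and reported smoking) is kept intact and respondents' own smoking status is reassigned at random among respondents, many times. Equivalently, use one row per respondent and compare the share of contacts who smoke between smoking and non-smoking respondents.
- Keep whole-network random labelling only for the sub-network of ties in which both people are respondents reporting their own smoking.
- In The survey, state that respondent-reported relationships are nested within respondents.

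The cost is a small change to the permutation code and a few sentences, with no new data. Evidence for clustering on the share statistic becomes somewhat weaker. Bias from smokers over-reporting smoking contacts remains and should be acknowledged when results are interpreted.

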#### Sample size

A minimum sample size of 102 participants was determined. This sample size is sufficient to obtain 90 per cent power to detect a 10 per cent reduction in smoking between the pre-intervention group (36%) when compared with the post-intervention group. The current population smoking rate is based on data obtained from the 2008 National Aboriginal and Torres Strait Islander Social Survey (NATSISS) relating to the ACT Indigenous Australian population [87].

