**Methods and design:**

Our prospective study will use a mixed-method approach (qualitative and quantitative), including a pre- and post-test evaluation of a tobacco control initiative. The study will explore the social and cultural context underlying Indigenous Australian tobacco use and associated factors which influence smoking behaviour. Primary data will be collected via a panel survey, interviews and focus groups. Secondary data will include de-identified PBS items related to smoking and also data collected from the Quitlines call service. Network analysis will be used to assess whether social networks influence smoking behaviours. For the survey, baseline differences will be tested using chi^2^ statistics for the categorical and dichotomous variables and t-tests for the continuous variables, where appropriate. Grounded theory will be used to analyse the interviews and focus groups. Local Aboriginal community controlled organisations will partner in the study.

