## Methods/design

### Aim and objectives

The objectives of the research are to answer the following questions:

•do individuals' social networks influence smoking behaviours;

•is there an association between various social and cultural factors and being a smoker or non-smoker; and

•do the tobacco control programs under the Action Area 1 of the ACT Aboriginal and Torres Strait Islander Tobacco Control Strategy 2010–2014 (this includes smoking cessation groups, youth and community health promotion programs and education campaigns) impact on tobacco behaviours, attitudes and beliefs in the Indigenous Australian population.

We will undertake surveys, focus groups and interviews in two waves approximately 12 months apart; pre- and post-implementation of the multi-component tobacco control initiative. This will assist to identify commonalities and disparities, assessing the effectiveness of program and further exploring socio-environmental mechanisms that influence tobacco use, attitudes and behaviours [81,82]. Data will be collected via:

1. surveys;

2. interviews;

3. focus groups; and

4. use of existing de-identified health data, for example, the Talking About the Smokes survey data, data regarding relevant Pharmaceutical Benefit Scheme (PBS) item listings related to smoking (e.g. item codes for nicotine replacements) and Quitlines call data and volume.

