#### The sample population

Participants will generally be Indigenous Australian people residing in the ACT region. The sample will include adults and children (12 years and above). Young people have been included to reflect the younger Indigenous Australian demographic profile and the early uptake of tobacco use in children [95,96].

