#### Analysis

Statistical and social network analysis will be used to characterise and describe the results, using multiple imputation of missing data prior to analysis [55,81]. In examining the association between various social factors, data will be aggregated and entered in SPSS, UCINET, NetDraw and Microsoft Excel for statistical and network analysis. In assessing if tobacco control programs have influenced behaviours, attitudes and beliefs in relation to smoking, analysis will incorporate common descriptive statistics and comparisons between the pre- and post-intervention groups. For example, comparisons between the pre and post-intervention groups will use X^2^ (categorical distributions) and T-tests (interval or ratio data). Bivariate associations between variables will be tested by X^2^ in analysing smoking type (daily smoker, occasional smoker, light smoker, social smoker, ex-smoker and non-smoker) by gender, age group, income group, education level, etc. Wilcoxon rank sum tests or Spearmans rank correlations will also be used depending on whether the variables are binary or ordinal. Multiple regression will be used to test whether individual variables are independently predictive of outcomes. Comparisons will be conducted across and between the sub-groups for both pre- and post-intervention [81,99]. Analysis will also include examining the data from the Fagerström Test for Nicotine Dependence questions in the survey for reductions in means scores, indicating reduced nicotine dependence. The higher the accumulated Fagerström score per participant, the more intense the participant’s physical dependence on nicotine [84]. Computations will be undertaken using SPSS and Microsoft Excel [83-85].

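### The 90% power claimed for 102 participants does not hold for the planned pre/post chi-square; only a linked, paired analysis under best-case assumptions reaches it

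*Protocol article*

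**What the plan says.** The Sample size paragraph under The survey reads: "A minimum sample size of 102 participants was determined". It continues: "This sample size is sufficient to obtain 90 per cent power to detect a 10 per cent reduction in smoking", the comparison being "between the pre-intervention group (36%) when compared with the post-intervention group". The 36% comes from a 2008 national survey of the same population. The paragraph gives no significance level, sidedness or test. It does not say whether the reduction is absolute or relative, or whether 102 is per wave or in total. It gives no assumption about uptake, relapse or loss to follow-up.

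The Analysis section of the survey says, as an example, that "comparisons between the pre and post-intervention groups will use X^2^ (categorical distributions) and T-tests (interval or ratio data". Smoking status is categorical, so the chi-square is the test that this text points to for the powered outcome.

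Other parts point to repeated measures on the same people. The abstract says: "Primary data will be collected via a panel survey, interviews and focus groups". The aims say: "We will undertake surveys, focus groups and interviews in two waves approximately 12 months apart". The end of the survey analysis says: "The pre- and post-test survey will be analysed using Analysis of Variance (ANOVA) on the gain scores and Analysis of Covariance (ANCOVA". No paired test for a proportion is named anywhere.

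**The concern.** A fall from 36% to 26% is a modest difference between two proportions. About a hundred people per group is far too few to detect it with 90% power in an independent-groups comparison. The power sentence speaks of two groups, and the analysis text names the independent-groups test, so the claim looked false on the protocol's own terms.

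This sentence is the only numerical justification for the size of the survey, and the survey carries the quantitative evaluation of the tobacco control programs. Under the chi-square as written, with 102 independent respondents per wave, a true 10-point fall would be missed about two times in three. A reader told that power was 90% would have no warning of that when weighing a non-significant result.

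**Working it through.** **Inputs.** From the protocol: N = 102, power 90%, baseline 36%, a 10 per cent reduction, chi-square between groups. Assumed because not stated: two-sided 5% (z = 1.960; z for 90% power = 1.2816). Both readings of the reduction (to 26%, or to 32.4%) and both readings of N (102 per wave, or 51 per wave) are shown.

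**1. The plan's figure under the chi-square named.** With p̄ the mean of the two proportions and δ their difference, the number per group is

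n = [1.960·√(2p̄(1−p̄)) + 1.2816·√(p₁(1−p₁)+p₂(1−p₂))]² / δ².

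- 36% vs 26%: p̄ = 0.31; the roots are 0.6541 and 0.6502; n = (1.2820 + 0.8333)² / 0.01 = 447.4, so 448 per wave.
- 36% vs 32.4%: n = 3,646.9, so 3,647 per wave.

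Power is Φ[(δ√n − 1.960·√(2p̄(1−p̄))) / √(p₁(1−p₁)+p₂(1−p₂))].

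- 36% vs 26%, 102 per wave: Φ[(1.0100 − 1.2820)/0.6502] = Φ(−0.418) = 33.8%.
- 36% vs 26%, 51 per wave: Φ[(0.7141 − 1.2820)/0.6502] = Φ(−0.873) = 19.1%.
- 36% vs 32.4%, 102 per wave: Φ[(0.3636 − 1.3149)/0.6704] = Φ(−1.419) = 7.8%.
- Difference detectable with 90% power at 102 per wave: about 19.7 points.

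The 90% is not reproduced. Other choices do not rescue it: for 36% vs 26% with 102 per wave, a one-sided 5% test gives 46%, one-sided 10% gives 60%, and the arcsine method 34%. A one-sample test against 36% gives 56%. Applying the unpaired chi-square to a linked panel of 102 gives 18% (no one moving into smoking) to 34% (no within-person correlation), by simulation.

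**2. Where 102 could come from.**

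*(a) Paired test.* For McNemar's test, let p₁₀ be the share who quit, p₀₁ the share who start or relapse (called uptake here), p_d = p₁₀ + p₀₁ and δ = p₁₀ − p₀₁ = 0.10. Then

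n = [1.960·√p_d + 1.2816·√(p_d − δ²)]² / δ².

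With p₀₁ = 0: (0.6198 + 0.3845)² / 0.01 = 100.9, so 101 pairs. Power at 102 pairs is Φ[(1.0100 − 0.6198)/0.3] = 90.3%. This matches the stated figure.

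*(b) Different effect.* 36% versus 10% by the arcsine method: h = 0.6435, n = 2·(3.2415/0.6435)² = 50.7, so 51 per group and 102 in total. That is a fall to 10%, not by 10 per cent.

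**3. How fragile reading (a) is.** Net fall 10 points, two-sided 5%, normal approximation; retention is applied to 102 (81.6, rounded to 82; 71.4, rounded to 71):

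| Uptake (quit) | 102 pairs (100%) | 82 pairs (80%) | 71 pairs (70%) |
|---|---|---|---|
| 0% (10%) | 90% | 83% | 77% |
| 2% (12%) | 78% | 68% | 62% |
| 5% (15%) | 62% | 53% | 47% |

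An exact McNemar test with 102 pairs gives 95%, 74% and 55% down the first column, which leads to the same conclusion. On the relative reading (net fall 3.6 points), McNemar with 102 pairs and zero uptake reaches only 48%.

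**The case against.** The strongest reply is that the design is a panel and a paired analysis is already planned. Gain scores require the same people at both waves, and the chi-square is offered only as an example. A gain-score test under the same best case (10% quit, none start, full retention) needs about 97 people for 90% power, and 102 gives about 91%. So the 90% can be reached within a type of analysis that the protocol names. This stands, and it limits the point. It does not remove it, for two reasons. The gain-score sentence does not say that it applies to binary smoking status, whereas the chi-square is assigned to categorical outcomes. The paired route also needs every favourable assumption at once, and none is stated.

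Four stronger readings are tempting, and the documents do not support them:

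- That the study's power simply is 34%. This figure belongs to one scenario: independent respondents, 102 per wave, absolute reduction, two-sided 5%.
- That the authors made an arithmetic slip. Two calculations give 102, so a mismatch with the stated test or a misworded effect is at least as likely.
- That zero uptake contradicts the enrolment of children from age 12. The protocol gives "early uptake of tobacco use in children" as a reason for including them, but no uptake rate and no share of the sample. The two are in tension, not in contradiction.
- That a null result would necessarily be read as program failure. The protocol plans to triangulate several data sources and concedes that a pre/post design is less robust, although it does not mention low power.

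**Conclusion.** Wrong as written. The stated 90% does not hold for the chi-square that the survey analysis names. With two-sided 5% assumed, power for 36% to 26% is about 34% with 102 independent respondents per wave and 19% with 102 in total. For a relative reduction it is about 8% with 102 per wave. About 90% is attainable only with linked participants, a paired test, a 10-point absolute fall, no uptake or relapse, and no loss over roughly 12 months. Modest departures from those conditions bring it to between 83% and 47% in the table above. That table counts complete pairs; the protocol plans multiple imputation, and any gain from it is not quantified here. The conclusion that the power sentence and the analysis text must be reconciled does not depend on which explanation of 102 is right.

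**What to change.** Keep 102 as the minimum and change two paragraphs.

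1. **Sample size.** State the significance level and sidedness, whether the reduction is absolute or relative, whether 102 is per wave or in total, the test, and the uptake and retention assumptions. Replace the single 90% with power across uptake of 0, 2 and 5% and retention of 100, 80 and 70%, as in the table above. If the intended effect was something else, such as a fall to 10%, correct the wording of the effect and recompute.
2. **Analysis.** For pre/post smoking status, replace the unpaired chi-square with McNemar's test on participants linked across waves, in line with the panel description and the gain-score analyses. Changing only the power sentence would leave the mismatch in place.

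If the waves will not be linked, keep the chi-square but state power of about 34% (102 per wave) or 19% (102 in total), and a detectable difference of about 20 points at 102 per wave.

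The cost is rewording, with no extra participants. The paired option depends on being able to match respondents between waves. The drawback is that the stated power becomes less favourable.
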